	**Number of subjects**
Total number of subjects selected	156
Number of centers	4
Inclusion period (months)	24

### Data collection, management, and analysis

#### Data management

Data are collected on paper and in an observation notebook (with all questionnaires), then entered by the research team on the secure CleanWEB® platform. This platform enables data to be downloaded, anonymized, stored and randomized.

### Statistical methods

The characteristics of all patients will be described globally and according to their randomization group, using the number of patients (%) for qualitative variables and the median [interquartile range] or mean (± standard deviation) for quantitative variables, depending on the normality of their distribution. A patient flow diagram will be generated. Results are reported according to CONSORT recommendations. Tests will be two-tailed, and a significance level of *p* < 0.05 will be considered statistically significant. The primary outcome (self-reported cumulative number of standard drinks consumed at 8 months) will be compared between the two groups using Student's t-test for independent samples. Complementary analyses will be conducted using generalized linear regression models adjusted for minimization factors and number of sessions per setting. Given the repeated measurement of outcomes and the multicenter design of the study, additional analysis will be performed including Cox and mixed models. To consider Survival analysis will also be conducted using a linear mixed model. Secondary endpoints will be analyzed using the same methodology as for the primary endpoint, i.e. a comparison of the mean using the usual tests. primary endpoint, i.e. a comparison of means using standard tests at 8 months. Secondary analyses to assess changes in secondary endpoints will be performed using evaluated using linear mixed models.

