
## Methods/Design

### Study setting and population

Study data will be collected in day hospitals (DH) within the addiction departments of public hospitals. For this research, four centers in the Paris area will be involved in recruiting patients. The four recruiting centers are: 1) Department of Addictions—Hôpital Albert Chenevier—CHU Henri Mondor—APHP – Créteil, 2) Department of Addictions—Hôpital Fernand Widal—Nord—Université de Paris—APHP – Paris, 3) Department of Addictions—Centre hospitalier des Quatre Villes – Sèvres, 4) Department of Addictions—Tolbiac Day Clinic – Paris. Recruitment will be done by the investigating physician at the time of admission to the DH during an individual consultation. If the patient is eligible for the study, the full protocol will be presented and reviewed during an individual consultation at the DH enrollment visit.

The following inclusion criteria apply: i) 18 to 80 years of age at the time of enrolment; ii) patients with a diagnosis of AUD according to DSM-5 criteria (American Psychiatric Association, 2013); iii) patients who had been abstinent for at least 15 days; iv) patients who can speak, understand and read French; v) patients who have signed an informed consent form and who are affiliated to a health insurance plan.

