### Treatment groups

The first four CBT group sessions focus on understanding the effects of alcohol, assessing motivation to change, behavioral and emotional strategies, cognitive strategies, relapse prevention and assertiveness strategies. These sessions are conducted in a group setting by a trained psychologist and a trainee.

Participants are then randomized into two groups (M1): i) VR-CET + BT group, ii) CBT group only. Allocation is centralized, individualized and randomized according to the following factors: center, presence of pharmacological treatment to maintain alcohol abstinence (2 modalities), history of AUD treatment in the last five years (2 modalities), alcohol consumption goals (2 modalities) and severity of alcohol dependence according to DSM-5 criteria (3 modalities).

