### Evaluation outcomes

#### Primary outcome

The primary outcome is the cumulative number of standard drinks consumed (in grams of pure alcohol) at 8 months, as reported by patients. As a reminder, in France, 1 standard drink = 10 g of pure alcohol = 1 unit of alcohol [25]. Alcohol consumption is estimated retrospectively by patients every month using the Timeline Follow-Back (TLFB) method, a widely used method that has demonstrated good psychometric properties and superiority over free recall [26]. This method allows retrospective estimation of alcohol consumption over a specified period of up to one year. Estimates of alcohol consumption (in standard drinks) are collected monthly by the research team, either in person or by telephone, to reduce recall bias and improve the performance of this method over time [27].

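### The primary t-test leaves out the five factors used to balance allocation, so it is conservative if they are prognostic; the factor-adjusted model should be primary

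*Protocol article*

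**What the plan says.** Four statements in the article bear on this point.

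- **Endpoint** (Primary outcome): "The primary outcome is the cumulative number of standard drinks consumed (in grams of pure alcohol) at 8 months, as reported by patients".
- **Allocation** (Treatment groups): "Allocation is centralized, individualized and randomized according to the following factors: center, presence of pharmacological treatment to maintain alcohol abstinence". The list continues with AUD treatment history, consumption goal and DSM-5 severity. Besides the four centres, the factors have 2, 2, 2 and 3 levels.
- **Primary test** (Statistical methods): the 8-month drink total "will be compared between the two groups using Student's t-test for independent samples".
- **Adjustment** (Statistical methods, next sentence): "Complementary analyses will be conducted using generalized linear regression models adjusted for minimization factors and number of sessions per setting". This is also where the allocation factors are called minimisation factors. Cox and mixed models follow as additional analyses, partly because the trial is multicentre.

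The only mention of distribution shape concerns descriptive summaries, which are chosen "depending on the normality of their distribution". No such condition is attached to the primary test.

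**The concern.** Balancing arms on prognostic factors removes part of the chance variation in the difference between arms. An unadjusted t-test does not take this into account: it estimates its standard error from the full between-patient variance, including the part that allocation has already balanced. The interval is then too wide and the p-value too large. The sponsor chose these five factors, and medication, consumption goal and severity are plausible predictors of drinking.

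The planned complementary model does not settle the matter. It is not the primary analysis, and it also conditions on number of sessions. Randomisation takes place at M1, after the four group sessions, so the individual sessions 5–8 come after it. The regression that adjusts for all five factors thus also adjusts for something the assigned arm may influence.

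At stake are the precision of the primary estimate and power in a trial sized for 80%. The validity of a positive result is not at stake.

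**Working it through.** **1. The plan's own figure.** Sample size gives 65 per group for power 0.80 at two-sided α = 0.05. No mean difference or standard deviation is stated, so 65 cannot be rebuilt from inputs, only solved backwards:

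- Normal approximation: d = (1.960 + 0.842) × √(2/65) = 0.491
- Noncentral t: d = 0.495

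I use d = 0.495, so the noncentrality is 0.495 × √(65/2) = 2.82.

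**2. Effect of balanced allocation.** Let the factors explain a share R² of outcome variance and be fully balanced. The true standard error is then √(1−R²) times the one the t-test reports. For R² = 0.10, 0.20 and 0.30 this factor is 0.949, 0.894 and 0.837, so the reported standard error is too large by about 5%, 12% and 20% (1/0.949, 1/0.894, 1/0.837). The article gives no R²; these are assumptions.

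**3. Formulas.**

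- True size of the t-test = 2 × [1 − Φ(1.96/√(1−R²))]
- Power, unadjusted = Φ((2.82 − 1.96)/√(1−R²))
- Power, adjusted = Φ(2.82/√(1−R²) − 1.96)

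| Assumed R² | True size of 5% t-test | Power unadjusted | Power adjusted |
|---|---|---|---|
| 0.10 | 3.9% | 82% | 84–85% |
| 0.20 | 2.8% | 83% | 88% |
| 0.30 | 1.9% | 85% | 92% |

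The first adjusted entry is 84.5% with d = 0.495 and 84.0% with d = 0.491.

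**4. Check by simulating minimisation.** Real minimisation balances imperfectly, so the five factors (4×2×2×2×3 levels) were minimised with a biased coin of 0.8 in 130 patients.

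- Normal outcome, 2,500 runs, in-sample R² of about 0.15, 0.34 and 0.52: t-test size was 4.8%, 3.0% and 0.6%. Fitting eight indicators inflates in-sample R². The degrees-of-freedom correction 1 − (1−R²) × 129/121 gives about 0.10, 0.30 and 0.49. Power was 81%, 84% and 86% unadjusted, against 83%, 93% and 98% adjusted.
- The adjusted test's size in those runs was 5.6%, 6.1% and 4.1%. The Monte Carlo standard error is about 0.44 points (√(0.05 × 0.95/2500)), so these figures are noisy.
- A separate simulation with 3,000 runs at R² = 0.10, 0.20 and 0.30 gave t-test sizes of 4.0%, 2.6% and 2.2%, close to the formula.

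**5. Check with a skewed outcome.** The distribution is not stated, so these settings are illustrative.

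- Skew alone (20–60% zeros, log-SD 0.8–1.5, 65 per arm): t-test size ran from 5.1% down to 3.0%.
- Skew plus minimisation (in-sample R² about 0.11, 0.21 and 0.26): t-test size was 3.8%, 2.5% and 1.9%, against 4.3%, 4.0% and 3.6% adjusted. For drinkers' totals halved in one arm, power was 61%, 49% and 32% unadjusted, against 63%, 57% and 43% adjusted.

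In all these settings the t-test was conservative or close to nominal, and adjustment gained power.

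**The case against.** The strongest reply is that nothing here endangers the trial. The error is in the safe direction, so a significant t-test could be believed. Under the assumptions used, the unadjusted test still reaches 82–85% against a target of 80%. At R² = 0.10 adjustment adds under 3 points, and the article supports no particular R². An adjusted analysis is already planned, so the dispute is only about which analysis is primary. All of this stands, and it sets the weight of the point. It does not remove it: the primary analysis decides the trial's conclusion, and the planned adjusted model carries the post-randomisation session count.

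A reader might go further in three ways that the document does not support.

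- **That the t-test inflates false positives, or that the trial is underpowered because of it.** The calculations show size at or below about 5%, and power above the planned level at the stated 65 per arm.
- **That the plan ignores the allocation factors.** It adjusts for them, but not in the primary analysis.
- **That the outcome is known to be zero-heavy and the t-test is therefore invalid.** Entry requires "patients who had been abstinent for at least 15 days". That makes zeros and a long right tail a reasonable expectation for an 8-month total, but the article states no distribution and 15 days of abstinence does not establish one. With equal arms of this size, the t-test's type I error held up under skew. A linear model of the raw total would not recover efficiency lost to skew either; its gain comes from the factors.

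**Conclusion.** The point holds as a matter of precision. The primary comparison omits the five factors on which allocation is balanced. If those factors are prognostic, the test is conservative and its interval too wide. For an assumed R² between 10% and 30%, true size falls to between 3.9% and 1.9%, and the power forgone is roughly 3 to 7 percentage points at 65 per arm.

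That the primary test is unadjusted is certain from the text. The size of the loss is not: it rests on an R² the article does not give, an effect size solved backwards from 65 per group, and allocation that balances the factors well. This should be changed, but leaving it would not make the trial's result unsound.

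**What to change.** In Statistical methods, keep the stated endpoint, the cumulative standard drinks at 8 months, and replace the primary test as follows.

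- **Primary:** a linear model of that total on arm, centre, abstinence medication, AUD treatment history, consumption goal and DSM-5 severity. Number of sessions is left out. This still estimates a difference in mean drinks.
- **Inference:** because right skew is likely, use robust standard errors, a bootstrap, or re-randomisation that replays the minimisation algorithm. Name one in advance.
- **Sensitivity:** the present t-test.
- **Support:** a count model such as negative binomial, with the same five factors.

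The cost is a wording amendment and a little programming. No new data are needed, since the factors are already recorded for allocation. If the sponsor treats the change as substantial, the article's own procedure of sponsor approval and an ethics committee opinion applies. As the trial is open-label, the change should be dated before any comparison of outcomes by arm.

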### Study design and procedure

This study is a multi-center, randomized, controlled trial involving two parallel groups: i) the VR-CET group, which benefits from virtual reality exposure preceded by CBT sessions, and ii) the CBT-only group (control group). Interventions take place over a 2-month (8-week) cycle, with a total of 8 sessions (Cf. Figure 1). Both groups receive 4 CBT group sessions in the first month, followed by either 4 supervised individual virtual exposure sessions for the VR-CET group, or 4 additional individual CBT sessions for the CBT-only group. Each session lasts one hour and a half. Once the 8 sessions have been completed (2 months), patients are followed up for 6 months, for a total of 8 months.

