#### CBT treatment group

Individual CBT sessions (sessions 5 to 8 in the control group) are conducted by a CBT-trained investigator and focus on reviewing and adapting the strategies discussed in the group sessions. The sessions last between 30 and 90 min and are designed to develop a list of strategies adapted to the patient's daily life, addressing various environments such as the supermarket, parties, home and exposure to advertising. The patient's desire to drink is regularly assessed using a visual analog scale (VAS).

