#### VR-CET treatment group

For the VR-CET group, individual exposure sessions (sessions 5 to 8) are conducted by an investigator trained in CBT. Prior to the exposure sessions, each patient will establish a hierarchy of four virtual environments: exposure to alcohol advertising, home, supermarket, and parties (cf. Figure 2) ranging from the simplest to the hardest. The duration of exposure to each virtual environment varies according to the time needed to reduce the participants’ craving. Participants move on to the next environment when a comfortable level of emotion or craving is reached, and exposure can be repeated if necessary. If craving remains high at the end of a session, it is extended. After exposure, patients benefit from a 5 to 10 min VR relaxation session. Craving is regularly assessed using a VAS before, during and at the end of each session.

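### The complementary regression adjusts for a session count that, on its natural reading, includes sessions 5 to 8 after randomisation, so its treatment coefficient can be biased and need not estimate the ITT effect

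*Protocol article*

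**What the plan says.** All places are in the protocol article.

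- **Primary analysis (Statistical methods).** Cumulative drinks at 8 months "will be compared between the two groups using Student's t-test for independent samples". No covariates enter. Selection of participants for analyses puts ITT first and per-protocol second.
- **Complementary analysis (Statistical methods).** "generalized linear regression models adjusted for minimization factors and number of sessions per setting". Neither the session count nor the word setting is defined.
- **Timing (Treatment groups).** The four group CBT sessions come first. Of these the article says: "These sessions are conducted in a group setting by a trained psychologist and a trainee". Then: "Participants are then randomized into two groups (M1").
- **After randomisation (Study design and procedure).** The group sessions are "followed by either 4 supervised individual virtual exposure sessions for the VR-CET group, or 4 additional individual CBT sessions for the CBT-only group".
- **Format of sessions 5 to 8.** In the VR arm, "individual exposure sessions (sessions 5 to 8) are conducted by an investigator trained in CBT". The control-arm section likewise describes sessions 5 to 8 as individual.

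**The concern.** A regression adjusted for baseline factors estimates the effect of assignment, with randomisation protecting the comparison. A regression that also holds fixed the amount of allocated treatment received does not.

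Two mechanisms matter. First, if sessions reduce drinking and one arm attends more of them, adjustment strips that part out of the treatment effect. Second, if an unmeasured factor such as relapse risk lowers attendance and raises drinking, then comparing arms at equal attendance compares patients with unequal relapse risk.

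Both need the arm to influence the count, and the article makes that possible. The section on discontinuing or modifying interventions allows temporary breaks for VR-related discomfort, which only one arm can have. A link between attendance and outcome is also plausible. The outcome accumulates over the 8 months from enrolment, so drinking during month 2 counts towards it and may itself reduce attendance at sessions 5 to 8.

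At stake is how the complementary result is read. Allocation uses five factors that the t-test ignores, and this is the one model the article states will adjust for them. A reader could well use it to support or question the primary result.

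**Working it through.** **Step 1: which sessions the covariate covers.** The plan is four group plus four individual sessions in both arms. A planned count is constant and could not serve as a covariate, so the count can vary only as sessions actually received. Treatment groups uses setting for delivery format (group), and sessions 5 to 8 are called individual. Sessions per setting therefore most naturally means group sessions received and individual sessions received. With randomisation at M1, the group count is pre-randomisation and harmless, and the individual count is post-randomisation.

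**Step 2: the formula.** In a linear model with arm and session count S only,

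adjusted effect = unadjusted effect − g × ΔS,

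where ΔS is the difference in mean sessions between arms (VR minus control) and g is the within-arm slope of outcome on sessions. If ΔS = 0 or g = 0, adjustment changes nothing.

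**Step 3: five scenarios.** None of these inputs comes from the article. They are: 156 patients, 3000 runs, outcome in approximate SD units (negative means less drinking), and S ~ Binomial(4, p) with logit p = 1 + aT·arm + aU·U. In A to D the latent factor U adds 0.5 per SD to the outcome, which is 25% of its variance.

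| Scenario | Unadjusted | Adjusted for S |
|---|---|---|
| A. True effect 0, arm does not affect S, U lowers S | −0.002 | −0.002 |
| B. True effect 0, VR lowers S (aT = −1), U lowers S | −0.007 | −0.22 |
| C. True effect 0, VR raises S (aT = +1), U lowers S | 0.004 | +0.18 |
| D. True effect 0, VR lowers S, U does not affect S | −0.001 | −0.002 |
| E. Direct effect −0.30, VR raises S, each session −0.2 | −0.42 | −0.30 |

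Hand checks:
- B: mean sessions are 2.00 against 2.79, so ΔS = −0.79. With g = −0.28, the shift is −(−0.28)(−0.79) = −0.22.
- C: ΔS = 0.59 and g = −0.30, so the shift is +0.18.
- E: mean sessions are 4 × 0.881 = 3.52 against 4 × 0.731 = 2.92, so ΔS = 0.60. The total effect is −0.30 + (−0.2)(0.60) = −0.42, and the adjusted model returns only −0.30.

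**Step 4: sensitivity to the shared cause.** True effect 0, logit p = 1.2 + a·arm − u·U, with a = ±0.4 or ±0.8 and u = 0.5 or 1.0. The arms then differ by about 0.25 to 0.66 of four sessions.

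| Outcome variance explained by U | Absolute bias of adjusted effect (SD) |
|---|---|
| 10% | 0.04 to 0.11 (smallest value 0.036) |
| 20% | 0.05 to 0.15 |
| 69% | 0.09 to 0.28 |

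All values lie between 0.03 and 0.28 SD. The sign follows the sign of a. With a = 0 the bias is zero within simulation error. The unadjusted difference is about zero throughout.

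**Step 5: separate counts.** If VR sessions and individual CBT sessions enter as two covariates, they nearly determine the arm. In scenarios A to E the standard deviation of the treatment estimate rises from about 0.16 to between 0.37 and 0.76.

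**Step 6: comparison with the planned effect.** Sample size gives no difference or SD. Back-solving from 65 per group at two-sided 0.05 and power 0.80 gives (1.960 + 0.842) × √(2/65) = 0.49 SD. This is an inference from the sample size, not a stated target.

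**The case against.** **The primary result is untouched.** It is an unadjusted t-test under ITT, and the criticised model is labelled complementary. This stands and limits the severity. A reader might infer that the trial's main comparison is compromised, but nothing in the article supports that.

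**The wording is ambiguous.** The article does not say sessions attended, and "Study setting and population" uses setting for the study site. The full protocol or SAP, not shown here, may define the term. A per-centre reading is possible but less likely, because the planned number is fixed at 4 + 4. Half of the covariate on the natural reading, the group-session count, is legitimate. Both points stand.

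**Bias is not inevitable.** A reader might infer that the adjusted estimate is biased. Scenarios A and D show none when the arm does not affect attendance, or when attendance neither shares a cause with drinking nor affects it. The article has no attendance data to say which case applies. A temporary break for VR discomfort need not mean lost sessions, and extending a session changes its length, not the count.

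**The larger figures need strong assumptions.** A bias of 0.28 SD requires a latent factor explaining about 69% of outcome variance. The minimisation factors in the model may also carry some relapse risk. If they acted as a proxy sharing 30% of the latent factor's variance (assumed), the bias would fall by about a fifth to a third.

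**Other models are planned.** A reader might infer that this is the only adjusted between-arm analysis. Cox and mixed models are also named, with covariates not stated, so that is unproven.

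What remains is that the article names a covariate which, on its natural reading, is partly post-randomisation. That is a stated choice rather than detail left to an SAP.

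**Conclusion.** The point holds in conditional form. On the natural reading, the complementary model conditions on receipt of the allocated treatment, so randomisation does not protect its treatment coefficient and the coefficient need not equal the ITT effect. It can show a benefit or harm that is not there, or remove the part of a real effect that runs through attendance.

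With a true effect of zero and attendance differing by arm, the bias is about 0.03 to 0.15 SD if the shared cause explains 10 to 20% of outcome variance, and reaches 0.28 SD at about 69%. With no arm difference in attendance it is zero. These figures rest wholly on assumed inputs and a linear model in SD units, and a model with another link would give other numbers.

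Severity is moderate: a supportive analysis is affected and the primary ITT t-test is not.

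**What to change.** In Statistical methods, limit adjustment in the complementary regression to the minimisation factors and variables fixed before randomisation at M1. The count of group sessions 1 to 4 may stay if it is defined as such. Remove the count of individual sessions 5 to 8.

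If the effect of session dose is of interest, specify it as a separate analysis labelled exploratory. It should not rely on assignment as an instrument unless the exclusion restriction is justified. Assignment to VR also replaces the four individual CBT sessions, so it is doubtful that assignment acts only through VR sessions received.

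The cost is one phrase, with no new data and no change to sample size or the primary analysis. It should be done before outcome data are seen by arm, since a later change of covariates would look data-driven.

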Virtual reality exposure therapy (VR-CET) is a new therapeutic exposure technique that uses virtual reality (VR) to allow users to navigate and interact with a computer-generated (and computer-maintained) three-dimensional environment in real time through a headset [15]. The advantages of this technique are the therapist's control over the exposure, the freedom to stop exposure at any time if necessary, the possibility of adapting the virtual environment to the subject's problems, and better observation of the patient's reactions. All these elements promote greater immersion and interaction of the patient with the virtual environment than, for example, exposure in imagination, another typical technique used in CBT [16]. Moreover, technological advances in recent years have made it widely available, easily accessible, simpler to use, better tolerated, and increasingly less expensive. Several studies report promising results for VR-CET in the treatment of various mental disorders [16], including addictive disorders [17]. The use of virtual reality was motivated by the fact that many patients were reluctant to experience violent anxiety-provoking situations in vivo during CBT sessions [18]. Thus, the application of VR-CET has been extended to many other specific phobic disorders (acrophobia, arachnophobia, social phobia, claustrophobia, agoraphobia,etc.) and has shown a therapeutic effect superior to no intervention and equivalent to exposure through standard techniques [18–20]. For people suffering from excessive alcohol consumption, VR-CET has been shown to be effective in inducing and reducing craving [21]. Despite this promising advance, there remains a gap in the data on the efficacy of VR-CET in maintaining abstinence or reducing alcohol consumption, which remain the primary goals of therapeutic interventions. This raises the need for further studies to shed light on this area of research. The primary objective of this study is to evaluate the efficacy of a treatment strategy combining VR-CET and CBT on reducing the cumulative number of standard drinks (sd) of alcohol at 8 months after enrollment. Secondary objectives are to evaluate the efficacy of the same treatment strategy on reducing alcohol craving, anxiety, depression, and rumination, and on increasing self-efficacy at 8 months. This article describes, in accordance with SPIRIT standards [22] and following the CONSORT [23] declaration checklist A prospective, comparative, randomized, open-label, 8-month clinical trial (2 months of therapy followed by 6 months of follow-up) with two parallel groups: i) VR-CET + CBT, ii) CBT alone without exposure (control group). This was a national multicenter study involving four addictology centers. A total of 156 patients diagnosed with AUD according to DSM-5 criteria were included.

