## Discussion

The present study aims to evaluate the efficacy of VR-CET combined with CBT in the treatment of AUD in recently abstinent individuals. A recent review of the literature highlights the emergence of virtual reality as an innovative and promising tool in the therapeutic landscape [21]. Studies on the efficacy of VR-CET have mainly focused on craving, with findings such as that exposure to alcohol-related stimuli in virtual reality can increase participants' desire to drink [5]. In terms of its reduction, VR-CET appears to have positive effects, particularly for individuals with AUD [1, 41]. The perceived level of realism of the virtual environment seems to influence this efficacy, with a more pronounced reduction in the desire to drink when the environment is perceived as realistic. About anxiety, the effects of VR-CET were mixed, but integration with CBT resulted in a significant reduction in post-treatment anxiety, although less favorable than in the CBT group alone. About alcohol use, only one study examined this variable and showed that VR-CET had no significant short-term effects [42]. The systematic review highlighted the lack of longitudinal data to consolidate the efficacy of VR-CET as a therapeutic tool to reduce alcohol consumption Table 2.

Our protocol aims to address the limitations of previous research by increasing the sample size (*N *= 156), by aiming not only for abstinence but also for a reduction in consumption, which seems more realistic, by having broad inclusion criteria to allow the inclusion of a population as close as possible to clinical reality, integrating sociodemographic questions into our inclusion questionnaire, and considering comorbidities via the MINI questionnaire at inclusion. In addition, we included urinary toxicity test (ethyl glucuronide) during the two months of therapy to objectify alcohol use data. In response to previous criticism regarding the lack of virtual environments with negative connotations, two neutral environments (subway and supermarket) were included to induce a sense of stress.

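### The survival analysis is assigned to a linear mixed model, which does not handle censored event times, and no time-to-event outcome is listed for it or for the Cox model named beside it

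*Protocol article*

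**What the plan says.** All references are to the protocol article.

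- **Statistical methods, primary analysis.** The primary outcome "will be compared between the two groups using Student's t-test for independent samples". Generalized linear models adjusted for the minimisation factors and the number of sessions follow as complementary analyses.
- **Statistical methods, additional analyses.** Because outcomes are measured repeatedly and the trial has several centres, "additional analysis will be performed including Cox and mixed models". The next sentence opens with a broken fragment and continues: "Survival analysis will also be conducted using a linear mixed model".
- **Primary outcome.** "The primary outcome is the cumulative number of standard drinks consumed (in grams of pure alcohol) at 8 months, as reported by patients". This is a quantity, not an event time.
- **Secondary outcomes.** Craving (questionnaire and visual analogue scale), AUDIT-C, anxiety, depression, self-efficacy, rumination, presence in virtual reality and cybersickness. None is a time to an event.
- **Introduction, objectives.** The primary objective is efficacy "on reducing the cumulative number of standard drinks (sd) of alcohol at 8 months after enrollment". The secondary objectives are efficacy "on reducing alcohol craving, anxiety, depression, and rumination, and on increasing self-efficacy at 8 months".
- **Sample size.** 65 patients per group, raised to 78 (156 in total) for an assumed drop-out of 20%.

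**The concern.** A survival analysis needs a method that separates patients who had the event from patients whose observation stopped before it. A linear mixed model makes no such distinction. If its response is an observed time, a patient lost at month 3 without drinking enters exactly as a patient who first drank at month 3.

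The Cox model in the preceding sentence would make the distinction. However, the article attaches no event, time origin or censoring rule to it, and the reason given for using it (repeated measurement and several centres) does not identify one.

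What is at stake is one supplementary result. An analyst who follows the text either produces an invalid estimate or has to decide later what the survival analysis was meant to be.

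**Working it through.** No figure in the article decides this point. It rests on setting the statements side by side. A short calculation under stated assumptions then shows when the wording would do harm.

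**1. Method against task.** The only sentence that assigns a method to the survival analysis names a linear mixed model. The sentence before it names Cox and mixed models together. A Cox model handles right-censoring and a standard linear mixed model does not. Read literally, the second sentence adds a further analysis with an unsuitable model. Read as a damaged edit, it swaps the two methods' roles. It needs correcting on either reading.

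**2. Outcome against method.** The primary outcome is an amount consumed. The secondary outcomes are scores, scales and questionnaire results. None is defined as the time to an event.

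**3. Time origin.** Under Study setting and population, patients must have been abstinent for at least 15 days at entry. Under Treatment groups, they are randomised at M1, after the four group sessions. The primary objective counts 8 months from enrolment. A drink taken between enrolment and M1 would be an event before randomisation if the clock starts at enrolment, and needs a rule if it starts at M1. A corrected sentence must therefore state the origin.

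**4. Expected early loss.** With the article's own drop-out assumption, 0.20 × 156 = 31.2, so about 31 patients would have incomplete follow-up.

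**5. When the wording does harm.** The inputs below are assumptions, because the article gives no event rate or hazard ratio:

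- first-drink hazard of 0.15 per month in controls;
- hazard ratio 0.6, hence 0.15 × 0.6 = 0.09 per month in the other group;
- exponential times over the 7 months from M1 to M8;
- the linear model's response is the observed time.

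With drop-out hazard d, the mean observed time up to 7 months is (1 − exp(−7(h + d))) / (h + d).

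| Drop-out by month 7 | d per month | Control mean (months) | VR-CET mean (months) | Difference (months) |
|---|---|---|---|---|
| 0% | 0 | (1 − exp(−1.05))/0.15 = 4.33 | (1 − exp(−0.63))/0.09 = 5.19 | 0.86 |
| 20% | −ln(0.8)/7 = 0.0319 | 3.96 | 4.71 | 0.75 |

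With no drop-out, the difference of 0.86 months is the true difference in restricted mean time to month 7. Capping at the end of follow-up alone therefore causes no bias in that quantity. With 20% drop-out, equal in both groups, the difference falls by 0.86 − 0.75 = 0.11 months, about 13%. The harm comes from loss before M8, not from patients who are still abstinent at M8.

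**The case against.** The strongest reply is that the sentence is visibly damaged. It begins with an unfinished fragment, and the same paragraph contains an orphaned repeat and a doubled verb. The likeliest intention was Cox models for survival and mixed models for repeated measures. The event definition for an additional analysis may also sit in the full protocol or the SAP, which are not shown. Most of this stands. It makes the error a probable slip, and it means the missing definition alone would not be a finding. It does not make the printed sentence right, because that is the only place where a method is assigned to the survival analysis.

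A further objection is that the sentence names no response variable. A mixed model fitted to monthly consumption would have no event times to mishandle. That is true, and it is why the calculation above is conditional. Such a model would, however, not be a survival analysis.

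Three stronger readings are tempting and are not supported:

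- **The trial's abstinence question has no valid analysis.** The Introduction says "there remains a gap in the data on the efficacy of VR-CET in maintaining abstinence or reducing alcohol consumption", and the Discussion describes the protocol as addressing earlier limitations "by aiming not only for abstinence but also for a reduction in consumption". These are rationale and commentary. Abstinence is not among the formal objectives. A suitable model is named, and nothing prevents reporting zero drinks from the TLFB data.
- **An abstinence endpoint must be added.** This would be a preference, not the correction of an error.
- **The bias is large, because mean times capped at 7 months differ far less than uncapped means.** That contrast compares two different quantities, one extrapolated beyond follow-up and the other a legitimate restricted mean. It does not measure bias.

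**Conclusion.** The point holds, and it is minor. As printed, the survival analysis is assigned to a method that does not handle censoring, while a suitable method is named one sentence earlier and neither has a listed time-to-event outcome. Only a supplementary analysis is affected. The primary t-test, the sample size, the intention-to-treat analysis and the comparisons of secondary means do not rest on it.

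The conclusion about the wording needs no numerical assumption. Any statement of size does. The 0.11-month shrinkage depends on the assumed hazards, on exponential times, and on 20% drop-out that is equal between groups and unrelated to drinking. It shows the mechanism and does not predict the trial's result.

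**What to change.** Replace the sentence with text to this effect:

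> Time from randomisation (M1) to the first drink reported on the TLFB after M1 will be analysed with a Cox model that allows for centre, as a stratum or a frailty term. Patients without such a drink will be censored at their last TLFB contact or at M8. All randomised patients are included, whether or not they drank before M1. Linear mixed models will be used for repeated measures only.

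If the full protocol or the SAP already defines the event, origin and censoring rule, use that definition and correct only the method named here.

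The cost is one sentence and one variable derived from the monthly TLFB data already collected. No new data collection and no change to the primary analysis or sample size are needed. The correction should be made before outcome data are compared between the groups.
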